# Testing the Impact of Phone Texting Reminders for Children's Immunization Appointments in Rural Cameroon: Protocol for a Nonrandomized Controlled Trial

**DOI:** 10.2196/47018

**Published:** 2023-08-09

**Keywords:** immunization, children, Cameroon, digital health, global health, nonrandomized controlled trial, child vaccination

## Abstract

**Background:**

Globally, over 20 million children are unvaccinated and over 25 million missed their follow-up doses during the COVID-19 pandemic; thus, they face vaccine-preventable diseases and unnecessary deaths. This is especially the case for those with HIV or living in vulnerable settings. Using cell phones to send reminders to parents has been shown to improve vaccination rates.

**Objective:**

We aim to determine whether implementation of an automated SMS reminder will improve child vaccination rates in a turbulent, semiurban/semirural setting in a low-income country.

**Methods:**

This will be a nonrandomized controlled trial that will be conducted at Azire Integrated Health Centre, Bamenda, Cameroon.

**Results:**

A total of 200 parents per study group (aged over 18 years) who are registered at the clinic at least one month prior to the study will be recruited. The intervention group will receive 2 reminders: 1 week and 2 days prior to the scheduled vaccination. For those who miss their appointments, a reminder will be sent 1 week after their missed appointment. The control group will receive the regular care provided at the clinic. Baseline information, clinical visit data, and vaccination records will be collected for both groups. Descriptive statistics will be used to summarize baseline characteristics between and within clusters and groups. The Fisher exact test will be used to compare parent-child units who return for follow-up visits (as a percentage) and children vaccinated as scheduled (as a percentage) between the study groups. Finally, we will compare how many members of both study groups return for 1 follow-up visit using Kaplan-Meier survival analysis.

**Conclusions:**

Due to limited effective child vaccination interventions in unstable settings, this study will be of high importance for suggesting a holistic approach to improve child vaccination and public health.

**International Registered Report Identifier (IRRID):**

DERR1-10.2196/47018

## Introduction

Child immunization is a key component of the World Health Organization (WHO) and United Nations Children’s Fund (UNICEF) child survival intervention package [1]. Immunizing children is an essential strategy in primary health care services and a crucial public health objective. Yet internationally, there are up to 19.4 million children who are still unvaccinated and face unnecessary deaths [2], including an especially high number of children living either in resource-limited settings or living with HIV. Therefore, children are considered a high-risk group for acquiring vaccine preventable diseases (VPDs) Also, the WHO and UNICEF warn of an increased number of missed follow-up doses for children due to the COVID-19 pandemic since 2020; over 25 million children have missed their follow-up doses. Such a decrease in child vaccination is considered a serious threat to the health of children, especially children living with HIV, in comparison to their immunocompetent similar-aged peers [3].

The vaccination system in Cameroon, including the administration of follow-up doses, has been weakened, and herd immunity has been compromised. In September 2022, the government of Cameroon announced a strategy to promote immunization among zero-dose children [4]. In 2021, UNICEF reported that different regions of Cameroon face the challenge of low vaccination coverage for several reasons, including armed conflict, insecurity, and underfunding of national vaccination programs [1]. Using cell phones to send reminders to parents about vaccination appointments has been shown to support adherence [5,6].

In 2019, we tested a smartphone app called Children Immunization App (CIMA) at a refugee camp in northern Jordan [6]. CIMA was developed to record the vaccination history of children according to the Jordanian national vaccination guidelines, provide health education information, and generate automated reminders for parents. The app was specially designed to target people with low literacy, with consideration of usability and technical concerns in a marginalized context [2]. CIMA was tailored to meet the needs of the target population. The messages and visuals were all customized to fit the local context [2].

In 2021, in collaboration with the University of Yaoundé and the United Nations Office on Drugs and Crime (UNODC) [7], we modified the CIMA functions. The penetration of smartphones is low in Cameroon; therefore, installing CIMA for parents would create a large selection bias. However, non-smartphone cell phones have an estimated penetration of over 95% [8]. Therefore, we have modified the app so information is saved locally in the clinic and reminders and health education messages are sent in the form of SMS texts to the registered cell phone numbers of the parents. We used English and French messages in order to fit the needs of the Cameroonian context. The main aim of this study is to implement an automated SMS system at Azire Integrated Health Centre, Bamenda. The objective is as follows: analyze the effect of the cell phone reminder intervention on the percentage of parent-child units returning for follow-up visits and the percentage of children receiving immunization as scheduled.

## Methods

### Study Setting

The study will be conducted at Azire Integrated Health Centre, Bamenda. Bamenda is located in the northwestern part of Cameroon (known for the volcanic Bamenda Highlands). Bamenda is considered a cosmopolitan town, with an area of 5250 km^2^; it includes 7 subdivisional councils and over 800,000 inhabitants. Since 2016, a sociopolitical crisis has been ongoing in Bamenda and it has become a turbulent zone. Today, it is estimated that over 95% of households in Bamenda own at least one cell phone.

The national vaccination schedule for children takes place during the first 11 months after birth at 5 clinic visits. The first contact is at birth and includes (1) the bacillus Calmette-Guérin (BCG) vaccine again tuberculosis and (2) the oral polio vaccine (OPV). The second contact is at 6 weeks and includes vaccination against diphtheria, tetanus, pertussis, hepatitis B, *Haemophilus influenzae* type b (DTP-HepB-Hib), OPV, pneumococcal infections (pneumococcal vaccine [PCV] 13 and rotavirus vaccine 1). The third contact is at 10 weeks and includes DTP-HepB-Hib, OPV, PCV 13, and rotavirus vaccine. The fourth contact is at 14 weeks and includes DTP-HepB-Hib, OPV, inactivated poliovirus vaccine, PCV 13, and rotavirus vaccine. The fifth contact is at 9 months and includes vaccination against measles, rubella, and yellow fever. Additionally, vitamin A is given during months 6 to 11 (Table 1) [9]. This study aims to assess the impact of an automated reminder at the second contact appointment.

The team members have different areas of expertise: epidemiology and the usefulness of digital tool reminders for clinic appointments for vaccination [3-5], the usefulness of telemedicine [6], adherence to taking antiretroviral treatment on time using cell phone reminders [7], and insulin supply pickup using SMS versus phone call reminders [8]; all members are experts in the study context of Bamenda and Cameroon.

**Table 1 table1:** Vaccination schedule for children during the ages of 0 to 11 months in Cameroon.

Contact (age), vaccine			Preventable disease		Route of administration
**First contact (birth)**					
	Bacillus Calmette-Guérin vaccine	Tuberculosis		Intradermal	
	OPV^a^ 0	Poliomyelitis		Oral	
**Second contact (6 weeks)**					
	DTP-HepB-Hib^b^ 1	Diphtheria, tetanus, pertussis, infection due to *Haemophilus influenzae* type b, hepatitis B		Intramuscular	
	OPV 1	Poliomyelitis		Intramuscular	
	PCV^c^ 13 1	Pneumococcal infections		Oral	
	Rotavirus 1	Rotavirus diarrhea		Intramuscular	
**Third contact (10 weeks)**					
	DTP-HepB-Hib 2	Diphtheria, tetanus, pertussis, infection due to *Haemophilus influenzae* type b, hepatitis B		Intramuscular	
	OPV 2	Poliomyelitis		Intramuscular	
	PCV 13 2 ; rotavirus 2	Pneumococcal infections; rotavirus diarrhea		Intramuscular; oral	
**Fourth contact (14 weeks)**					
	DTP-HepB-Hib 3	Diphtheria, tetanus, pertussis, infection due to *Haemophilus influenzae* type b, hepatitis B		Intramuscular	
	OPV 3; IPV	Poliomyelitis		Oral; intramuscular	
	PCV 13 3	Pneumococcal infections		Intramuscular	
**Fifth contact (9 months)**					
	Measles, rubella	Measles, rubella		Subcutaneous	
	Yellow fever	Yellow fever		Subcutaneous	

^a^OPV: oral polio vaccine.

^b^DTP-HepB-Hib 1: diphtheria, tetanus, pertussis, hepatitis B, Haemophilus influenzae type b.

^c^PCV: pneumococcal vaccine.

### Sample Size

The current proportion of children returning back on time to complete their immunization in the clinic is estimated to be around 75%. We therefore aim to improve participation in the intervention clinic. With a study power of 80%, α=.05, and β=.2, we need to recruit a total of 400 participants (at a 1:1 ratio, ie, n=200 participants per study arm). We will include patients lost to follow-up in an intent-to-treat analysis strategy.

### Inclusion and Exclusion Criteria

All registered parent-child units who fulfill the following inclusion criteria will be invited to participate in the study: (1) registration at the clinic within the past month at the time of the study; (2) subsequent immunization scheduled for newborns; (3) parents aged more than 18 years; (4) at least one parent owns a cell phone, and (5) residency in the northwestern province. Potential participants will be excluded if the baby is coming for its second or later immunization visit or if the parents are not residents of the northwestern province.

### Intervention and Control Groups

The recruitment will be done through two steps. In step 1, the intervention group will be recruited. Then, in step 2, when the sample size is achieved, recruitment of the control group will be conducted until we reach the required sample size.

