## Results

Study enrollment was planned for the beginning of 2023. Usually, the clinic schedules child vaccination 2 days per week (Tuesdays and Thursdays). Approximately 20 of 50 babies are newborns and receive their first-contact vaccine (Table 1). This means that we estimate that we will need to approach 40 of 100 parents per week to explain the study and ask for consent. We estimate we will recruit a total of 200 babies in each study group during a total period of 5 weeks (pending the response rate per week of the parents). Therefore, the total duration of recruitment might be between 10 and 12 weeks.

We expect to complete the study by July 2023 and complete the data analysis and submission of the final report by 2024. We include a dummy example of how the data will be visualized for the vaccination clinic site (Figure 1). The general characteristics of the babies in both study groups are presented in a table, including the characteristics of the babies that did not come back to the clinic. The Kaplan-Meier survival analysis will be shown as a figure.

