### Limitations

We foresee the following points as potential limitations of our planned study: (1) The language context of the study is predominantly English, so the study may not be generalizable to the rest of Cameroon, where French is spoken. (2) We plan to test the effect of the SMS reminders for 1 vaccination appointment only, so further studies will be needed to ensure effectiveness over longer periods of time (for example, to ensure that parents will not have SMS fatigue). (3) The scalability of the SMS reminders needs to be evaluated from a cost-effectiveness perspective to ensure that we can provide an estimated cost for policymakers if the Ministry of Health of Cameroon scales the project (however, we performed a cost-effectiveness analysis for the CIMA-Jordan project and found that the cost was low in the context of a low-income country [20]). (4) Bamenda is considered a turbulent location due to the current crisis; this might affect the study if the situation becomes more turbulent. Such situations, labeled “armed conflicts,” are known strongly impact childhood vaccination [21], as they may lead to either forced migration of the parents out of Bamenda or short-term closure of the Azire Integrated Health Centre.

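### All intervention babies are enrolled before the first control at a single clinic, so arm is confounded with calendar period and the planned comparison cannot isolate the reminder effect

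*Protocol article*

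**What the plan says.** The Intervention and Control Groups section sets a strict order: "In step 1, the intervention group will be recruited. Then, in step 2, when the sample size is achieved, recruitment of the control group" begins and runs until its own target is met. There is one site; Study Setting states: "The study will be conducted at Azire Integrated Health Centre, Bamenda". The abstract calls the study a nonrandomized controlled trial.

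On timing, the Results section states: "We estimate we will recruit a total of 200 babies in each study group during a total period of 5 weeks". It puts total recruitment at 10 to 12 weeks. The outcome visit is the second contact at 6 weeks of age (Study Setting, Table 2).

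Data Analysis compares baseline characteristics, then the key measures by Fisher exact test, then attrition, then return for one follow-up visit by Kaplan-Meier. It states no adjustment for time, no concurrent comparator and no pre-study series.

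Limitations, item 4, says: "Bamenda is considered a turbulent location due to the current crisis; this might affect the study if the situation becomes more turbulent". It adds that armed conflict may lead to forced migration or a short closure of the health centre. It does not say that such an event could fall on one arm only.

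**The concern.** The stated objective is causal: to analyse the effect of the reminders on return and on-schedule immunisation. When every intervention appointment falls in one period and every control appointment in the next, anything that changes between the periods enters the arm difference in full. It can look like a benefit, look like harm, or hide a real benefit. Collecting the baseline questionnaire does not help, because family characteristics carry no information on whether the clinic was open or the roads were safe in a given week.

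This is not a detail that an analysis plan could settle later. The design is stated explicitly, and no analysis of these two groups can create overlap in time.

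**Working it through.** **1. Calendar windows.** Inputs: about 40 newborns per week over two clinic days, 5 weeks per group (Results); second contact at 6 weeks.

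- Enrolment: 40 × 5 = 200 per group, if nearly every parent approached agrees. Intervention about weeks 0-5, control about weeks 5-10.
- Scheduled second contact, adding 6 weeks: about weeks 6-11 and 11-16.
- At 12 weeks of recruitment (6 per group): about weeks 6-12 and 12-18.

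The scheduled windows meet only at the boundary week.

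**2. Identification.** Let b be the on-time rate under usual care in the control period, d the SMS effect, and s the difference between the periods (intervention minus control) under usual care. The expected rates are b + d + s (intervention) and b (control), so the expected difference is d + s. Two means cannot identify three quantities, and a period term would be collinear with arm. Kaplan-Meier does not help, because its clock is time within child and not calendar time.

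**3. What 200 per arm can detect.** Sample Size gives a current rate that "is estimated to be around 75" percent, and states: "With a study power of 80%, α=.05, and β=.2, we need to recruit a total of 400 participants". No target rate is given, so the figure cannot be reproduced directly and has to be solved backwards (two-sided, pooled variance):

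n = [1.96 √(2p̄q̄) + 0.842 √(p₁q₁ + p₂q₂)]² / (p₂ − p₁)²

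For 75% vs 86%: p̄ = 0.805, numerator (1.098 + 0.467)² = 2.45, divided by 0.0121, gives 203 per arm. With continuity correction, 75% vs 86.5% gives 201, and exact Fisher power at 200 per arm is then 80.3%. The implied detectable gain is thus about 11 to 11.5 points. This is a back-calculation, not a figure in the article.

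**4. Sensitivity to an assumed period shift.** Exact enumeration of the two-sided Fisher test, 200 vs 200, intervention period at 75%, no SMS effect:

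| Control-period rate | P<.05 | Direction |
|---|---|---|
| 75% (no shift) | 3.8% | either |
| 70% | 17.3% | false benefit |
| 65% | 54.9% | false benefit |
| 80% | 18.9% | false harm |
| 85% | 66.5% | false harm |

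With a true effect of 86% vs 75%, Fisher power is 76%. If the control period runs 5 points higher for other reasons (86% vs 80%), it falls to 31%. If 10 points higher, a benefit is declared in about 3%.

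**5. A short closure.** One week closed in a 5-week appointment window touches 1/5 of one arm's appointments. If every displaced visit counts as not on time, the loss is 0.20 × 75% = 15 points. That is an upper bound for the on-time measure. It shrinks if displaced families return soon enough to count, and the return measure might only be delayed.

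**The case against.** The design is openly labelled nonrandomized, the windows are short and adjacent, and item 4 of the limitations names the crisis and how it could act. No passage supports a shift of 5 or 10 points between two neighbouring 5-week blocks. All of this stands, and it means that the figures above show sensitivity and not expected bias. It does not remove the confounding: lack of randomisation is a different matter from lack of concurrency, and item 4 treats instability as a threat to the study as a whole.

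The article gives the study's expected completion as July 2023 and is dated August 2023, so on its own timetable a new allocation scheme may come too late. That bears on which remedy is still open, not on whether the point holds.

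Four stronger readings are tempting, and the documents do not support them:

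- That the protocol expects closures or migration. The wording is conditional: these may happen.
- That enrolling controls while the SMS system is running contaminates them. Reminders go to phone numbers registered for the intervention, and the Control Group section rules out SMS and educational messages for controls. Concurrent enrolment would also run alongside the SMS system.
- That there was no reason for two blocks. An article condenses the full protocol, and the rationale may be there.
- That enrolling controls first would cure the problem. The arms would still occupy different periods.

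**Conclusion.** The point holds for the design and analysis as written. Arm and calendar period coincide at one clinic, the Fisher and Kaplan-Meier comparisons cannot tell them apart, and the limitations do not say so. It affects the study's only between-group comparison.

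Its size is unknown. Under assumed shifts with no SMS effect, a control period 5 or 10 points below 75% turns a 3.8% rejection rate into about 17% or 55%. A shift the other way produces apparent harm or masks a real gain. A one-week closure could cost up to 15 points of on-time attendance under the worst-case counting rule, which exceeds the roughly 11 to 11.5 points that 200 per arm can detect. The conclusion itself rests on none of these figures, only on the recruitment order, the single site and the visit timing.

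A reader might infer that the trial's result will be biased, or biased in favour of SMS. The documents support neither. They support only that a reminder effect could not be distinguished from a period effect.

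**What to change.** **Preferred.** Replace steps 1 and 2 with one concurrent enrolment stream of 400. Allocate each baby at enrolment from a computer-generated permuted-block list. Keep 200 per arm and the 10-12 week recruitment period, and update the design label, which would no longer be nonrandomized. This is practicable because CIMA already schedules reminders per child, and the study ID and card sticker already show the arm. The cost is an allocation list and revised protocol and consent wording. The downside is that parents in the same sessions may talk about the messages, which could dilute the effect somewhat.

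**If clinic days are allocated instead.** Account for clustering by day, and do not fit the allocation unit as a fixed effect, since it would be collinear with arm. Expect some loss of precision: with about 20 newborns per day, the design effect is 1 + 19 × ICC. Assumed ICCs of 0.005 and 0.02 give 1.095 and 1.38, so 400 babies carry the information of about 365 and 290.

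**If the two blocks are kept.** State the arm-by-period confounding as a limitation, and say that closure or displacement could fall on one arm only. Use clinic-register attendance before and during both blocks to check for drift, preferably at visits the intervention does not touch. The 9-month contact is one example, since no enrolled baby reaches it within these windows. Such a check can reveal a large shift but cannot prove that there was none. Limit the conclusion to an association between consecutive periods, not an effect of the reminders. The cost is register extraction and more cautious wording.

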### Intervention Group

Study participants in the intervention group will receive the CIMA automated reminders on their cellphones. Messages will be sent to them to remind them of their appointments. Also, the CIMA system will provide educational information to the parents based on the parenting skills materials from the UNODC [7,10].

After obtaining informed consent, we will give each baby a study ID number that starts with the letter *I* (for “intervention”) and a continuous ID number that starts with the number 1001. Then, we will write the study ID number on a sticker that will be placed on the vaccination card of the newborn, so we can identify the baby in later visits as being enrolled in the CIMA intervention study group. For example, the first baby that will be enrolled in the intervention group will be given the ID number I-1001 and the last baby will have the ID number I-1201.

After the newborn receives the first vaccine, the vaccination nurse provides the parent an appointment date for the second contact vaccine. Then, we will record the appointment date in the CIMA database and schedule an automated reminder for the parents that will be sent at two time points: (1) 1 week before the appointment and (2) 2 days prior to the second contact appointment date. For example, if the second contact appointment date is scheduled for a Thursday, the automated SMS reminder will be sent out on the Thursday of the previous week and on the Tuesday of the same week. The content of the message will be as follows: “Dear parent, this is a kind reminder for the vaccination appointment of your child, scheduled on Thursday [date] at the Azire Integrated Health Centre.” This message has a total of 150 characters and can thus fit in 1 SMS; SMS messages have a maximum number of characters of 160. When the parents come to the second contact appointment, we will be able to identify enrolled newborns by the sticker that was placed on the vaccination card. We will record the date of arrival at the second contact appointment in the CIMA database. Each week, we will auto-generate a list of newborns that have missed their second contact appointment, and we will send a reminder to the parents about missing the appointment. The content of the message will be as follows: “Dear parent, your child has missed the vaccine appointment this week. You are requested to come as soon as possible to the Azire Integrated Health Centre”; this message includes a total of 153 characters and can fit into 1 SMS.

Each week, the parent will receive one SMS that has an educational message on parenting skills. We will use the UNODC parenting skills toolkit [9], which was tested in the past with CIMA in Jordan [10]. The last SMS educational message will be sent out on week 4 of the study (Table 2).

**Table 2 table2:** Overview of the action plan for the intervention and control groups.

			Study week													
			0^a^		1	2		3		4		5		6^b^		7

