### Control Group

Participants in the control group will continue to receive regular routine messages from the health facility. After obtaining consent, we will use the same procedure to give ID numbers to the babies in the control group, except that the letter *C* (for “control”) will be used instead of *I*. The control group will receive usual care at the clinic. For example, the vaccination nurse will review the schedule of vaccine appointments at the end of the month, then call parents that have missed their baby’s appointment to remind them about the second contact vaccine appointment and to invite them to come back to the clinic. No educational messages and no SMS reminders will be sent out to the participants enrolled in the control group.

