## Discussion

### Anticipated Findings

Child immunization is a crucial public health objective and an essential strategy in primary health care services. However, globally, there are still millions of children who are unvaccinated and at risk for VPDs. Prior to the COVID-19 pandemic, the effectiveness of automated reminders for children attending vaccination appointments was tested either by the team members of this project in the context of a refugee camp in Jordan [6,7] and the general community in Canada [3] or by other authors in Ethiopia [11], Nigeria [12], and other contexts [13,14].

The COVID-19 pandemic has also led to an increase in the number of missed follow-up doses for children. In Cameroon, the vaccination system has been weakened, and herd immunity is compromised. Also, UNICEF has warned about the impact of spreading false information (known as misinformation) about national vaccination programs in Cameroon [15]. The spreading of misinformation is considered one of the major threats to public health interventions, especially during and after COVID-19.

In this paper, we described version 1.0 of a study protocol for a nonrandomized controlled trial of child vaccination reminders in a turbulent, semiurban/semirural setting in a low-income country. The main goal of the study is to implement an automated SMS reminder system at the Bamenda primary health care center. The objectives of the study are to analyze the effect of the cellphone reminder intervention on the percentage of parent-child units returning for follow-up visits and the percentage of children receiving immunization as scheduled. Instability in northwestern Cameroon makes it important to improve childhood vaccination, and to the best of our knowledge, this is the first study to support a national vaccination program by (1) using an automated system to send reminders in the form of SMS messages and (2) send health educational messages about vaccines, as well as about parenting skills. Ames et al [16] found that childhood vaccination communications have focused on national campaigns against polio, instead of routine vaccination programs. Therefore, we think this study might have the secondary impact of promoting routine vaccination among parents.

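### The stated aim is the effect of SMS reminders, but the intervention arm also gets four weekly educational SMS before the outcome, so the comparison can address only the combined package versus usual care

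*Protocol article*

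**What the plan says.** **Effect named.** The title begins "Testing the Impact of Phone Texting Reminders". The abstract's objective is to determine "whether implementation of an automated SMS reminder will improve child vaccination rates". The Introduction's objective is to "analyze the effect of the cell phone reminder intervention on the percentage of parent-child units returning for follow-up visits" and on the percentage of children immunized on schedule; Anticipated Findings repeats it in nearly the same terms. Study Setting gives the purpose as assessing an automated reminder at the second contact. The Limitations speak of testing the SMS reminders' effect. The abstract's account of what the intervention arm receives lists reminders only.

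**Intervention delivered.** The Intervention Group section schedules two reminders before the appointment, one week and two days ahead, and a further SMS to parents who miss it. It then adds: "Each week, the parent will receive one SMS that has an educational message on parenting skills". It also states: "The last SMS educational message will be sent out on week 4 of the study". Table 2 has four ticks in the educational-message row and marks week 6 as the second contact.

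**Control.** "No educational messages and no SMS reminders will be sent out to the participants enrolled in the control group". The same section says controls continue to get the facility's routine messages and, at the end of the month, a nurse's call if the appointment was missed.

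**Content of the education.** The Intervention Group section describes parenting-skills material from a UNODC toolkit. Anticipated Findings says the study will "send health educational messages about vaccines, as well as about parenting skills".

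**The concern.** The objective asks a question about one component, while the arms differ in two. A difference in attendance at the second contact could come from the reminders, from four weeks of additional contact and information, or from both. If the messages also cover vaccines, as the Discussion says, they have a plausible route of their own to attendance. The Discussion itself calls misinformation a major threat, and the Conclusion expects the study to help share correct information with parents.

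At stake is the main conclusion. Reported under the present title and objective, a positive result would be read as evidence that reminders alone raise attendance, and the Limitations discuss the scalability of the reminders in those terms. A programme that adopted reminders without the educational messages would be relying on an effect this trial does not estimate.

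**Working it through.** The protocol states no figure on this point to reproduce. The check is a count of components by arm, then a look at what the planned analysis can identify.

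**Step 1: scheduled contacts by arm** (Intervention Group, Control Group, Table 2)

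| Component | Intervention | Control |
|---|---|---|
| Educational SMS, weeks 1 to 4 | 4 | 0 |
| Reminder SMS before the appointment | 2 | 0 |
| Missed-appointment SMS | Yes, if missed | No |
| Usual care described for the arm | Not itemized | Routine facility messages; end-of-month call if missed |

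**Step 2: timing.** The last educational SMS is in week 4 and the second contact is at week 6. All four therefore precede the outcome visit. The missed-appointment SMS cannot affect on-time attendance, but it can affect later return, which is one of the two key measures and the subject of the Kaplan-Meier analysis.

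**Step 3: identification.** Let R = 1 if a family gets reminders, E = 1 if it gets educational SMS, and A = 1 for the intervention arm. By design R = E = A for every family. Setting confounding aside, the arm difference D in the proportion attending is

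D = d_R + d_E + d_RE

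where d_R is the effect of reminders alone, d_E that of education alone, and d_RE their interaction. The data supply one quantity, D, for three unknowns. There is no arm with R = 1 and E = 0, or the reverse. The Data Analysis section compares the two arms only, and no further modelling could separate components that never occur apart.

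**Step 4: illustration.** Sample Size gives an on-time rate of about 75% and 200 per arm at 80% power, but no target rate. Assume a target of 86%, which is about what that size detects (two-sided 5% test without continuity correction: 203 per arm needed, 79.5% power at 200). Then D = 86 − 75 = 11 points. With no interaction, two possible splits are:

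- reminders 8.25 + education 2.75 = 11 points
- reminders 2.75 + education 8.25 = 11 points

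Both give 86% versus 75%, so the trial's data would look the same. This demonstrates that the split is not identified. It does not estimate either part.

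**The case against.** The best reply is that the protocol openly describes a package. The Introduction says the app was modified to send both reminders and health education by SMS, and gives the main aim as implementing an automated SMS system. Anticipated Findings lists the two functions side by side. The Conclusion plans to expand CIMA itself, which is what is being tested. On this view, reminder intervention is shorthand for the system, and package versus usual care is a legitimate pragmatic contrast.

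Much of that stands. The educational component is disclosed, and nothing is wrong with testing a package. The shorthand reading does not carry the whole document, however. No section defines the term that way. The abstract's objective, the abstract's description of the intervention and Study Setting all refer to reminders only. The Limitations do not mention that the components cannot be separated.

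A reader might go further and infer that education probably explains most of any effect, because more educational messages than reminders are sent before the visit. The documents do not support that: message counts are not effect sizes, and the reminder texts state the appointment's date and place. A vaccine-education route rests on one Discussion phrase that differs from the Methods. Nor are controls without contact, given the routine messages and end-of-month calls.

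**Conclusion.** The point holds as one of labelling and attribution. Reminder and education are completely confounded with arm, so the planned tests can address only the combined CIMA SMS package against usual care. The size of the misattribution cannot be stated, because the design provides no information on the split. This rests on the schedule in the Intervention Group section and Table 2 being followed, and on controls receiving no study SMS.

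Two limits apply. First, this does not make the package comparison invalid, and the documents give no ground for saying that the education was concealed. Second, restating the objective does not make the package effect unconfounded: the intervention group is recruited in full before the control group, without randomization, so calendar time remains a separate problem.

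The correction should be made, since the plan as written leads to a conclusion the design cannot support and changing it costs almost nothing.

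**What to change.** 1. Restate the title, the objectives (abstract, Introduction, Study Setting, Anticipated Findings) and the conclusions as the effect of the CIMA SMS package versus usual care. Name the parts: weekly educational messages, two pre-appointment reminders and a missed-appointment reminder. Describe usual care as the Control Group section does. Add the educational messages to the abstract's description of the intervention.
2. Add to the Limitations that the reminder's own effect cannot be separated from that of the educational messages.
3. Reconcile the Intervention Group section (parenting skills) with Anticipated Findings (vaccines as well as parenting skills), so that readers know what the package contained.

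Sample size, data collection and analysis are unchanged. The cost is a narrower claim: the trial could no longer be presented as a test of reminders alone.
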